### Secondary outcomes for children

The *Strengths and Difficulties Questionnaire (SDQ)* is a widely used 25-item parent-rated questionnaire to measure behaviour, emotion, and adjustment of children aged 2 to 17. A total of five subscales were measured, including emotional symptoms, conduct problems, hyperactive-inattention, peer relationships, and prosocial behaviour. Each item is scored by the parent as follows: Never = 0, Somewhat True = 1, or Definitely True = 2. The scores for hyperactivity, emotional symptoms, conduct problems, and peer problems can be summed to generate a total difficulties score ranging from 0 to 40, whereas the prosocial score is not incorporated in the reverse direction into the total difficulties score. Higher scores in the total difficulties or subscales measuring child difficulties reflect greater difficulty levels, while higher scores in the prosocial behaviour subscale reflect greater child strengths. The Chinese version of the SDQ has been tested and validated in Chinese parents, teachers, and students (aged 6–15 years), including those with and without ADHD. Internal consistency for most factors across the parent-, teacher-, and self-report versions was moderate to high (Cronbach's  $\alpha = 0.55$ – $0.86$ ), with the exception of a lower  $\alpha$  for the 'Peer Problems' factor in the self-report

version ( $\alpha = 0.40$ ). Four-week test–retest reliability was satisfactory (intraclass correlations = 0.67–0.91).

All the measurement tools are valid and reliable in both original English and translated Chinese versions and have been approved for use.

#### **5.2.11 Data collection procedure**

Primary and secondary outcomes will be assessed at baseline (T0), immediately post-intervention (T1), and six months post-intervention (T2). All quantitative data will be collected via an online questionnaire platform (WJX.com) with support from a trained research assistant (RA) who will be blinded to group allocation.

**Baseline data collection.** After obtaining written informed consent, baseline data—including demographics and all primary and secondary outcomes—will be collected. During baseline, an RA will provide in-person assistance to participants who experience any difficulty using the online platform.

**Post-intervention data collection.** The RA will contact and remind participants in both groups via WeChat, telephone, and/or email to complete post-intervention assessments at the designated time points. At T1, participants in the intervention group will complete questionnaires for all primary and secondary outcomes and an intervention satisfaction form within one week after completing all sessions. During the same period, participants in the control group will complete the same set of outcome questionnaires (without the satisfaction form). At T2 (six months post-intervention), the RA will contact/remind participants in both groups to complete follow-up assessments for all primary and secondary outcomes. At all three

time points, the RA will be available via WeChat and telephone to assist participants who encounter difficulties during data collection. The RA will review submitted questionnaires on the survey platform immediately after submission and will contact participants to complete any missing items when needed.

#### **5.2.12 Data analysis**

Data analysis will be conducted in R software (Version 4.4.1 for Mac). Descriptive statistics will summarize sample characteristics and study outcomes. Assumptions of normality and homogeneity will be assessed when examining baseline group differences. Outcome analyses will use generalized estimating equations (GEE) under the intention-to-treat (ITT) principle to compare differential changes between groups across time points. All randomized participants will be retained in the models in accordance with ITT. Missing data will be handled within the GEE framework using robust standard errors, providing valid population-averaged estimates under Missing Completely at Random (MCAR) or Missing at Random (MAR) assumptions. When the proportion of missing data exceeds 10%, multiple imputation will be performed. If GEE results indicate significant effects, post hoc comparisons of estimated marginal means will be conducted to examine within-group and between-group differences for individual outcomes.

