### **5.2.5 Sample size estimation**

The effect size of parenting stress (primary outcome) was used to calculate the sample size. Our systematic review and meta-analysis found that the effect sizes of ACT-based interventions on reducing parenting stress in parents of children with autism were large, that is, Hedges'  $g = -1.25$  ( $n=20$ ) in Marion et al. (2021) and  $d = -5.81$  ( $n=60$ ) in Çiçek & Öncel (2023)

 at immediately post-intervention when compared with parent training or treatment-as-usual control group, respectively. The pooled effect size of parent-focused interventions in parents of children with autism also demonstrated a large effect size (Hedges'  $g=-1.26$ ) on parenting stress immediately post-intervention, when compared with the active/inactive control groups. However, given very limited studies of ACT-based interventions and relatively small sample sizes used, a medium effect size of 0.5 (Cohen's  $d$ ) on parenting stress was adopted to conservatively estimate the effects of this newly developed ACT-based parenting program for the parents caring for an autism child. Furthermore, attrition in RCTs can lead to biased treatment effect estimates, reduced statistical power, and limited generalizability . To determine the appropriate sample size, the expected attrition rate must be considered. Five of the included studies in the systematic review and meta-analysis had similar follow-up duration as this main RCT. The attrition rates ranged from as low as 0%  to as high as 59.65%. Therefore, to mitigate the risk of decreased statistical power, an average attrition rate of 16.9% was considered for the main RCT. Finally, taking into account the possible attrition rate of 16.90%, a total of 154 participants (77 per study group) were required for a statistical power of 80% and statistical significance of 5%, two-tailed, using G\*Power v. 3.1.9.7.

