#### **5.2.7 Randomization and concealment**

Eligible participants will be randomly assigned in a 1:1 ratio to either an ACT-based parenting program plus usual care (intervention group) or usual care only (control group), using permuted block randomization with variable block sizes of four or six. The allocation sequence will be generated by an online randomization program and administered by a research assistant (a registered nurse with a master's degree in nursing) who will not be involved in participant recruitment, intervention delivery, or outcome assessment. Group allocation will be concealed from outcome assessors, rehabilitation school teachers, parents, and children using sequentially numbered, opaque, sealed envelopes.

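### The outcome analysis is set as a difference in change with no stated baseline adjustment; using the T0 score as an adjuster would gain precision at almost no cost

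*Protocol*

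**What the plan says.** Section 5.2.12 of the Protocol names GEE under intention to treat as the outcome analysis, used "to compare differential changes between groups across time points". If the GEE result is significant, marginal means are then compared within and between groups. No covariate is named, and the section does not say whether T0 enters as a response or as a covariate. It also says: "Assumptions of normality and homogeneity will be assessed when examining baseline group differences".

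Section 5.2.11 measures outcomes at T0, T1 (immediately after the intervention) and T2 (six months after it). Baseline collection is described as "including demographics and all primary and secondary outcomes". Section 5.2.7 states that parents are "randomly assigned in a 1:1 ratio".

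Section 5.2.5 sizes the trial on "a medium effect size of 0.5" for parenting stress, "for a statistical power of 80% and statistical significance of 5%, two-tailed". It concludes: "possible attrition rate of 16.90%, a total of 154 participants (77 per study group) were required". It gives no correlation between visits and does not say whether the effect size is in units of the post-score SD or the change-score SD.

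**The concern.** The hypotheses in section 5.2.2 are worded as greater improvement, and section 5.2.3 calls the design repeated-measures. The natural reading of section 5.2.12 is therefore a model with T0, T1 and T2 as responses and an arm-by-time term. In such a model the arms may differ freely at T0, and the arm-by-time term is the between-arm difference in change.

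Randomisation makes the true baseline means equal, and that contrast does not use the fact. It subtracts the whole observed baseline difference, when only the part that predicts the follow-up score should be removed. The result is a wider confidence interval for the primary outcome than the collected data could give. The marginal-mean comparisons are made only after a significant GEE result, so the less precise contrast would also act as the gate to them.

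**Working it through.** **1. The plan's own figure.** Inputs from section 5.2.5: d = 0.5, two-sided 5%, 80% power, 16.9% attrition. A two-sample t-test (exact noncentral t) needs 64 per arm, with power 80.1%. Inflating gives 128 / (1 − 0.169) = 154.03, against the stated 154. In reverse, 77 × 0.831 = 63.99 completers per arm. The figure is reproduced by a plain two-group comparison with no baseline or correlation term.

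**2. Variance of each contrast at T1.** Take the SD as 1 at both T0 and T1, with correlation r. The variance of the between-arm difference is 2V/n, with n completers per arm, where:

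- post score alone: V = 1
- difference in change: V = 2(1 − r)
- baseline-adjusted: V = 1 − r²

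The gap between the last two is 2(1 − r) − (1 − r²) = (1 − r)², which is positive for every r below 1. As a proportion, the adjusted variance is (1 + r)/2 of the change variance, a reduction of (1 − r)/2. If the SDs are s0 at T0 and s1 at T1, the gap becomes (s0 − r·s1)². This is never negative, so the ordering does not depend on equal SDs, although the percentages do.

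**3. Numbers.** n = 64 per arm and d = 0.5 on the post-score SD. For r = 0.3 the standard error is √(2 × 1.40/64) = 0.209 for change and √(2 × 0.91/64) = 0.169 with adjustment. Power is from the exact t.

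| r (assumed) | V, change | V, adjusted | Variance reduction | Power, change | Power, adjusted |
|---|---|---|---|---|---|
| 0.3 | 1.40 | 0.91 | 35% | 66.0% | 83.7% |
| 0.4 | 1.20 | 0.84 | 30% | 72.7% | 86.5% |
| 0.5 | 1.00 | 0.75 | 25% | 80.1% | 90.0% |
| 0.6 | 0.80 | 0.64 | 20% | 88.1% | 93.9% |
| 0.7 | 0.60 | 0.51 | 15% | 95.2% | 97.6% |

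A simulation of 20,000 trials at r = 0.3, 0.5 and 0.7 gave 66.5%, 80.1% and 95.2% for change and 83.7%, 90.1% and 97.5% with adjustment.

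**4. What the gain is worth.** At r = 0.5, 64 completers per arm with adjustment give the precision of 64/0.75 ≈ 85 per arm analysed by change.

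**5. Where r matters.** Only the power of the change contrast can fall below the planned level through r. A between-arm comparison of T1 means without adjustment has V = 1 and power 80.1% whatever r is. The adjusted contrast has at least that power at every r. The same formulas apply at T2 with the T0–T2 correlation.

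**The case against.** **Model terms may be in an unseen statistical analysis plan.** This stands in part. A reader might infer that the marginal means are unadjusted. The protocol does not say so; it names no adjustment and excludes none. What the protocol does fix is a contrast of changes between groups, and the point rests on that.

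**No loss of planned power is shown.** This stands. A reader might infer from the table that the trial is underpowered. The total of 154 is reproducible, and the change contrast meets 80% once r is about 0.5 or more. If d = 0.5 was meant on the change-score SD, the dependence on r disappears. The effect sizes cited in section 5.2.5 were measured just after the intervention, which makes the post-score SD plausible, but the section does not say. Nothing in the protocol supports an r as low as 0.3 or 0.4. For other scales, section 5.2.10 reports four-week retest correlations of 0.67–0.91 (SDQ) and a weighted kappa of 0.88 (Psy-Flex). These are not T0–T1 correlations of parenting stress under treatment and are only indicative. At r = 0.67 the variance reduction is (1 − 0.67)/2 = 16.5%.

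**Chance imbalance does not bias the result.** This stands. The change contrast and the T1 or T2 difference are both unbiased under randomisation, and their standard errors already allow for chance imbalance.

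**The sentence on baseline differences is not evidence against adjustment.** This also stands. It concerns checking assumptions, and the section separately plans descriptive summaries. Nothing says that baseline checks replace adjustment or select covariates.

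**The covariate form has a drawback.** With only T1 and T2 as responses, a parent with T0 data alone contributes no row, yet section 5.2.12 keeps every randomised parent in the model. At 16.9% attrition that could affect about 154 × 0.169 = 26 parents. The fix has to deal with this.

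**Conclusion.** The point holds as one of efficiency. Section 5.2.12 sets a difference-in-change contrast and states no baseline adjustment, although the T0 score is collected for every outcome and randomisation equalises the true baseline means. Adjustment would reduce the variance at T1 by 35%, 25% or 15% at r = 0.3, 0.5 or 0.7. At d = 0.5 with 64 completers per arm, power would rise from about 66%, 80% or 95% to 84%, 90% or 98%.

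These figures assume equal SDs at T0 and T1, an effect size on the post-score SD, and an r that the documents do not give. The direction of the gain depends on none of these. The documents do not support the stronger conclusions that the sample size is wrong, that the analysis is biased, or that the marginal means are known to be unadjusted. If a statistical analysis plan already adjusts for baseline, one clarifying line in the protocol closes the point.

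**What to change.** In section 5.2.12, specify one of two forms:

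- **Preferred:** keep T0, T1 and T2 as responses, constrain the T0 means to be equal across arms, and use a non-independence working correlation. Under an independence structure the T0 scores would carry no information about the T1 and T2 differences, and the gain would be lost. This form keeps all randomised parents in the model.
- **Alternative:** take T1 and T2 as responses, with the T0 score of the same scale as a covariate and arm-by-visit terms. Use multiple imputation for parents with no follow-up, so that nobody randomised is dropped. The section already plans imputation above 10% missing data; for this form it should apply whenever a parent has no follow-up.

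Report the adjusted between-arm differences at T1 and T2 with 95% confidence intervals. In section 5.2.5, state whether d = 0.5 is on the post-score or the change-score SD and, if the change contrast is kept, the correlation assumed.

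The cost is one line of model specification, plus the imputation step if the covariate form is chosen. No new data and no extra participants are needed.

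### The protocol credits GEE with robust standard errors with validity under MAR, which it does not have in general; the 10% imputation trigger covers this only in part

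*Protocol*

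**What the plan says.** Protocol section 5.2.12 (Data analysis) makes GEE under intention-to-treat the analysis for all outcomes, including the primary outcome, parenting stress. On missing data it says they are "handled within the GEE framework using robust standard errors, providing valid population-averaged estimates under Missing Completely at Random (MCAR) or Missing at Random (MAR"). It then adds: "When the proportion of missing data exceeds 10%, multiple imputation will be performed". The 10% rule carries a citation (reference 73) whose title, as listed in the protocol, says that the share of missing data ought not to decide whether to impute.

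Section 5.2.5 (Sample size estimation) gives the expected loss: "an average attrition rate of 16.9% was considered for the main RCT". The similar trials it draws on had attrition from 0% to 59.65%. The design rests on "a medium effect size of 0.5" (Cohen's d). Assessments are at T0, T1 and T2 (section 5.2.11).

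**The concern.** The first sentence attributes to a method a property that it lacks. GEE solves unweighted estimating equations on the scores that were observed. These equations are unbiased if missingness is unrelated to the outcomes, or related only to covariates in the model. If dropout depends on an earlier observed score, which is the ordinary MAR case in a repeated-measures trial, they are biased in general. The exception is a working correlation that is essentially correct. The sandwich variance gives honest standard errors when the working correlation is wrong; it does not move the estimate back.

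The setting makes this more than a technicality. One arm attends eight weekly two-hour group sessions and the other receives usual care only, so the link between a parent's stress and staying in the study could plausibly differ by arm. The between-group contrast in parenting stress would then be biased while the protocol says that it is protected.

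The imputation sentence limits the damage but does not remove it. It leaves the incorrect claim in charge below the threshold, and it does not say of what the 10% is a proportion.

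**Working it through.** **1. The plan's own figures.** Inputs from section 5.2.5: d = 0.5, "a statistical power of 80% and statistical significance of 5%, two-tailed", attrition 16.9%, and "a total of 154 participants (77 per study group) were required"; allocation is 1:1 (section 5.2.7). A two-sample t-test needs 63.77, so 64 per arm (power 0.801). 2 × 64 / (1 − 0.169) = 128 / 0.831 = 154.03, which matches the stated 154. Keeping 64 of 77 is a loss of 13/77 = 16.9%. So the attrition figure acts in the design as a loss of participants.

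**2. Does the planned attrition trigger imputation?** It depends on the denominator, which the protocol does not give.

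| Pattern of loss | Per participant, or at T2 | Share of T0, T1, T2 | Share of T1, T2 |
|---|---|---|---|
| 16.9% at T2 only | 16.9% | 16.9/3 = 5.6% | 16.9/2 = 8.5% |
| 10% by T1, 16.9% by T2 | 16.9% | (10 + 16.9)/3 = 9.0% | (10 + 16.9)/2 = 13.5% |
| 16.9% by T1 and still at T2 | 16.9% | 2 × 16.9/3 = 11.3% | 16.9% |

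Counted per participant or at T2, imputation runs in every row. Counted over all planned assessments, it runs only in the last.

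**3. Size of the bias when imputation does not run.** The protocol gives no dropout mechanism and no within-person correlation, so these are assumptions: 10% lost at T2 in each arm; the odds of loss double per SD of the T1 score (b = ln 2 = 0.693); T1–T2 correlation ρ of 0.5 or 0.7; normal scores with SD 1.

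- Let z be the standardised T1 score within an arm and p(z) = expit(a + bz) the probability of loss. Setting the mean of p to 0.10 gives a = −2.38 and E[p(1 − p)] = 0.0860.
- For normal z, E[z·p] = b·E[p(1 − p)]. The mean of z among those still observed is therefore shifted by −0.693 × 0.0860 / 0.90 = −0.0662.
- The observed T2 mean is shifted by ρ times this: 0.5 × 0.0662 = 0.033, or 0.7 × 0.0662 = 0.046.
- With an independence working correlation and arm-by-visit means, GEE estimates the T2 mean by the observed mean, so the bias in the contrast is the difference between the two arms' shifts.

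| Dependence of T2 loss on T1 score | ρ = 0.5 | ρ = 0.7 |
|---|---|---|
| One arm only | 0.033 SD | 0.046 SD |
| Opposite directions in the two arms | 0.066 SD | 0.093 SD |
| Same in both arms | 0 | 0 |

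Against the target of 0.5 SD this is 0.033/0.5 = 7% to 0.093/0.5 = 19%. If the more stressed leave the intervention arm, the benefit is overstated; the reverse pattern understates it.

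**4. Role of the working correlation.** In large-sample simulations of the same scenarios, with exchangeable or first-order autoregressive true correlations, an exchangeable or correct working correlation left 0.01 SD or less. In a harsher setting (correlations 0.4, 0.3 and 0.8; logit slopes of 1 in opposite directions; 10% loss), independence gave 0.145 SD, a wrong exchangeable structure 0.06 SD and an unstructured one 0.007 SD. Imputation within arm on T0 and T1 was within simulation noise of zero.

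**5. The case where 16.9% is lost at T2 but counted as 5.6% or 8.5%.** The calculation in step 3 with 16.9% loss gives E[p(1 − p)] = 0.1314 and a shift of 0.693 × 0.1314 / 0.831 = 0.110. With independence, the bias is 0.5 × 0.110 = 0.055 SD (one arm, ρ = 0.5) up to 2 × 0.7 × 0.110 = 0.15 SD (opposite directions, ρ = 0.7).

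**The case against.** The strongest reply is the imputation sentence itself. A reader who stops at the first sentence might infer that the dropout the plan expects will bias the primary result. The protocol does not support that. Counted per participant, which is how section 5.2.5 uses the figure, or counted at T2, 16.9% exceeds 10% and the plan moves to multiple imputation. With arm and the earlier scores in its model, that is valid under MAR. This stands, and the bias at 16.9% in step 5 applies only if the threshold is counted over assessments.

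Three further points have force. First, the size depends on assumed dropout: with equal dependence in both arms there is no bias under any of the methods. Second, the larger figures need an independence working correlation. The protocol names no working correlation, and that choice commonly belongs in the SAP, as do the imputation model and the place of the imputed analysis. Their absence is not a fault here. Third, a well-chosen working correlation makes the bias negligible in most scenarios.

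None of this rescues the sentence as written. Where GEE comes close to validity under MAR, that is owed to the working correlation, whereas the protocol credits robust standard errors. And at or below the threshold the protocol offers nothing else.

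**Conclusion.** The point holds in a limited form. The stated property is wrong in general, and that conclusion needs no simulation. Its practical reach is the region where imputation is not triggered: missingness of 10% or less, or a denominator that keeps the figure below 10%. There, with 10% lost at T2, the bias is about 0.03 to 0.09 SD with an independence working correlation, about 0.01 SD or less with a near-correct one, and none when dropout depends on earlier scores equally in both arms. These sizes rest on an assumed odds ratio of 2 per SD and an assumed correlation of 0.5 to 0.7; the protocol gives neither, and the harsher assumptions in step 4 give more. It does not follow that the planned 16.9% attrition will bias the trial.

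The trigger is also badly fixed in its own right: the same losses can lead to either analysis depending on how they are counted, and the title of its cited source argues against a rule of this kind.

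**What to change.** In section 5.2.12:

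- State that unweighted GEE requires MCAR, or missingness that depends only on model covariates, and that robust standard errors address the variance only.
- Name one MAR-valid primary analysis, to be used whatever the proportion missing. Any of these serves: GEE after multiple imputation with arm and all earlier outcome scores in the imputation model; inverse-probability-weighted GEE; or a likelihood-based repeated-measures mixed model.
- Drop the 10% trigger, which also removes the question of its denominator.

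The cost is a change of wording and a little more analysis work with standard R routines; no new data are needed. A delta-shift sensitivity analysis for data missing not at random would be a reasonable option for the SAP, but is not part of this point.
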